### **Specific goals**

1. To compare the effects of the use a multifaceted intervention of environmental control in the ICU versus standard care, in quantity and quality of sleep by PSG and actigraphy, and by questionnaires, during the whole stay in ICU or up to day 30, and at hospital discharge and 6 months after ICU discharge.
2. To compare the effects of the use a multifaceted intervention of environmental control in ICU versus standard care, in the oscillation of plasma concentrations of Melatonin and Cortisol during the ICU at days 1 and 3 after randomization.
3. To compare the acute effects of the use a multifaceted intervention of environmental control in the ICU versus standard care, on prevalence and duration of delirium during ICU stay.
4. To compare the effects of the use a multifaceted intervention of environmental control in the ICU versus standard care, in neuropsychological impairment (depressive symptoms and cognitive impairment) at 6 months after ICU discharge.

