### **Secondary outcomes**

- 1) Total time of sleep assessed by actigraphy
- 2) Sleep quality assessed by questionnaires (RCSQ and PSQI)
- 2) Circadian timing: Oscillation of plasma concentration of Melatonin and Cortisol
- 3) ICU delirium (prevalence and duration of delirium in ICU) by Confusion Assessment Method for the ICU (CAM-ICU)
- 4) Neuropsychological impairment (depressive symptoms and cognitive impairment) at 6 months post ICU discharge by cognitive testing and instrument screens of depression

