#### **f. Study variables**

- 1. Baseline parameters to be collected:** At the time of enrolment, information collected on each patient will include the following: patient demographics, dates of hospital and ICU admission, illness severity according to the Acute Physiology (APACHE II), Chronic Health Evaluation II and Sequential Organ Failure Assessment Score (SOFA), comorbidities according to the Charlson Comorbidity Index, admission diagnoses, and pre-existing neuropsychological impairment.
- 2. Repeated assessments to be performed during the study protocol:** During the course of each patient's stay in the ICU data will be collected on: Sequential Organ Failure Assessment Score (SOFA), Partial pressure of oxygen (PaO2)/Fraction of inspired oxygen (FiO2), daily arterial pressure and minimum glycemia value obtained, daily doses of medications. Use of hemodialysis and vasopressors, mechanical ventilation duration and ICU/Hospital length of stay data will be collected also. All patients will undergo a standardized follow-up immediately prior to hospital discharge and at 6 months later. At 6 months patients will attend to a follow-up visit, and if they are unable to attend they will be visited at home.

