### ***Long term Neuropsychological impairment***

- Beck's Depression Inventory (BDI-II)(73): this instrument screens for depression using criteria consistent with the Diagnostic and Statistical Manual of Mental Disorders-Fourth Edition. Higher scores (range, 0-63) indicate more depressive symptoms. Based on testing in psychiatric outpatients, depression symptoms severity is classified as minimal score (score 0-13), mild (score 14-19), moderate (score 20-28) and severe (score 29-63). The BDI-II will be performed at hospital discharge and 6 months after ICU discharge.
- Repeatable Battery for the Assessment of Neuropsychological Status (RBANS)(74-76): The RBANS is a comprehensive and validated neuropsychometric battery for the evaluation of global cognition, including individual domains of immediate and delayed memory, attention, visuospatial construction and language. The RBANS will be performed at hospital discharge and 6 months after ICU discharge.

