### ***g. Sample size and statistical analysis***

According to a previous study, which measured sleep with PSG (63), and other studies, which have described sleep architecture in the ICU (3-7), we estimate that the N3 stage time in our study population will be 7 minutes with a SD of 9 minutes. We considered that a 50% improvement in N3 stage time would be both, clinically relevant and realistic. With a power of 80% and with alpha of 5%, we calculated that a sample size of 56 patients is required to demonstrate statistically significant differences.

General statistical analysis will be performed according to intention to treat. Baseline characteristics will be reported using mean values  $\pm$  standard deviation (SD), or median (p25-75) and proportions where

appropriate. The use of parametric vs non-parametric tests will be decided according to data distribution and the fulfillment or not of normality assumptions. Specific statistical analysis for comparisons between groups will be performed by Student's-t test or Mann-Whitney U-test for continuous variables, and by chi-square for proportions. Changes along time will be analyzed by one-way (repeated-measures) analysis of variance (ANOVA) or Friedman test. Interactions between groups and time we will assessed with two-way repeated-measures ANOVA. All statistical calculations will be performed using Stata Statistical Software, Release 15.1 (College Station, TX). A probability value (p-value) of less than 0.05 will be considered as statistically significant.

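### Six-month cognition and depression are compared without a baseline covariate although prior impairment is recorded at enrolment: valid, but gives up precision of unknown and possibly small size

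*Protocol*

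**What the plan says.** Specific goal 4 of the protocol compares the arms "in neuropsychological impairment (depressive symptoms and cognitive impairment) at 6 months after ICU discharge", and the last secondary outcome repeats it: "Neuropsychological impairment (depressive symptoms and cognitive impairment) at 6 months post ICU discharge". The instruments are the RBANS for cognition and the BDI-II for depression.

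The list of enrolment data in section III.f ends with "admission diagnoses, and pre-existing neuropsychological impairment". It names no instrument, scale or coding for that item.

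The section on long-term neuropsychological impairment fixes the assessment times: "The BDI-II will be performed at hospital discharge and 6 months after ICU discharge", and likewise "The RBANS will be performed at hospital discharge and 6 months after ICU discharge".

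Section III.g names the between-group tests: Student's t-test or "Mann-Whitney U-test for continuous variables, and by chi-square for proportions". It adds one further method: "Interactions between groups and time we will assessed with two-way repeated-measures ANOVA". The only stated use of enrolment data is descriptive: "Baseline characteristics will be reported using mean values" and similar summaries.

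**The concern.** Cognition and mood six months after intensive care depend partly on what the patient was like before admission. The protocol plans to record something about that before randomisation, but none of the analyses it names uses it. Variation between patients that was present on admission therefore stays in the error term. A chance excess of previously impaired patients in one arm would pass into the 6-month difference uncorrected.

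The trial is small: 56 patients, so 28 per arm at most, and fewer if some die or are lost by 6 months. The randomisation section states 1:1 allocation and mentions no stratification, so the design as written does not balance prior impairment either. Prespecification also matters, because adjusting only after an imbalance has been seen would be a data-driven choice.

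**Working it through.** **Inputs from the protocol.** Total 56, allocated 1:1, so 28 per arm; alpha 5%, taken as two-sided because the protocol does not say. The figure of 56 was set for N3 sleep time (3.5 min difference, SD 9 min), and no sample size is given for goal 4. It does not reproduce with the usual two-group formula: 2 × (1.960 + 0.842)² × (9/3.5)² ≈ 104 per arm. That is a separate matter; here 28 per arm is only the number of patients available.

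**Assumptions.** The correlation ρ between the enrolment item and the 6-month score, and retention of 20 per arm as an alternative. The protocol gives neither.

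**Step 1: which measurements precede randomisation.** RBANS and BDI-II are taken at hospital discharge and at 6 months, both after randomisation. The group-by-time ANOVA on these scores therefore contains no pre-ICU information. A discharge score may itself be affected by the intervention, so it cannot stand in for a baseline. The enrolment item is the only listed variable on prior neuropsychological status.

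**Step 2: unadjusted reference.** With 28 per arm (54 df), the t-test has 80% power for a difference of 0.762 SD. The standard error is √(2/28) = 0.267 SD, so the noncentrality is 0.762/0.267 = 2.85. With 20 per arm the difference is 0.909 SD.

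**Step 3: the same difference with one covariate.** The variance factor, including the cost of estimating the covariate, is f = (1 − ρ²) × (1 + 1/(2n − 4)). Power comes from the noncentral t distribution with 2n − 3 df and noncentrality d/√(2f/n).

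| Assumed ρ | f, 28 per arm | Power, 28 per arm | f, 20 per arm | Power, 20 per arm |
|---|---|---|---|---|
| none (unadjusted) | 1 | 80% | 1 | 80% |
| 0.15 | 0.9963 | 80% | 1.0047 | 80% |
| 0.30 | 0.9275 | 83% | 0.9353 | 83% |
| 0.42 | 0.8394 | 86% | 0.8465 | 86% |
| 0.50 | 0.7644 | 89% | 0.7708 | 89% |

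At ρ = 0.15 and 20 per arm, f exceeds 1 and power is 79.8%, a shade below the unadjusted test. At 28 per arm a gain of 5 points needs ρ of about 0.38.

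**Step 4: what ρ might be.** Suppose the item is a yes/no record with prevalence p, and impaired patients differ by D SD at 6 months. Then ρ² = p(1 − p)D² / (1 + p(1 − p)D²).
- p = 10%, D = 0.5: 0.0225/1.0225, so ρ ≈ 0.15.
- p = 30%, D = 1.0: 0.21/1.21, so ρ ≈ 0.42.

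Over this assumed range the gain runs from nil to about 6 points. A graded measure of pre-ICU function could do better.

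**Step 5: chance imbalance.** For a standardised baseline score, the chance that the arms differ by more than 0.3 SD is 2 × [1 − Φ(0.3/0.267)] = 2 × [1 − Φ(1.12)] = 0.26. An imbalance of exactly 0.3 SD moves the 6-month difference by ρ × 0.3: 0.09 SD at ρ = 0.3 and 0.15 SD at ρ = 0.5.

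**The case against.** The strongest reply is that nothing here is an error. A t-test, Mann-Whitney or chi-square test is valid for a randomised comparison, and covariates for secondary outcomes are often left to the SAP, which is not at hand. The covariate is also undefined. Patients are enrolled after at least 72 hours of invasive ventilation and no pre-ICU RBANS or BDI-II is scheduled, so a history item, possibly yes/no, is the likelier reading. A single such item would have to predict both cognition and mood. The exclusion of prior mental or intellectual disability and of primary neurological disease narrows its range further.

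Most of this stands, and it limits the size of the point. It does not remove it. The protocol names its between-group methods itself rather than deferring them, so the remark concerns a stated choice. A better use of data already planned is available for about one degree of freedom.

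A reader might infer more than the documents support:
- **That the comparison is biased.** It is not; randomisation protects it on average.
- **That a material imbalance is likely.** A 26% chance of exceeding 0.3 SD is not likely, and a shift of 0.09 to 0.15 SD is small beside a detectable difference of 0.76 SD.
- **That the trial's only long-term question is affected.** Goal 1 also follows sleep to 6 months, with the PSQI given then.
- **That adjustment would surely bring a sizeable gain.** Nothing in the protocol fixes ρ.

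**Conclusion.** The point holds as a matter of efficiency on a secondary outcome. As written, 6-month RBANS and BDI-II would be compared without using the one enrolment variable that bears on prior status. Compared with 80% power unadjusted, the benefit of using it ranges from none (ρ about 0.15) through about 3 points (0.3) and 6 points (0.42) to 9 points (0.5). These figures rest on assumed correlations, a roughly linear relation with the outcome, and 28 or 20 patients per arm. Where the trial falls in that range depends on how the item is recorded, which the protocol leaves open. The change is worth making because it is cheap and must be settled before the data are seen, not because the present test would mislead.

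**What to change.** In section III.g, prespecify that 6-month RBANS and 6-month BDI-II are each analysed by linear regression (ANCOVA) on arm, with the enrolment record of prior neuropsychological impairment as covariate, in the form in which it is recorded. Report the adjusted difference with its 95% CI, and keep the unadjusted test as supportive. State that hospital-discharge scores are not used as baseline. In section III.f, say how the enrolment item is recorded, since that determines what the adjustment can achieve.

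Do not make an adjusted logistic model the main analysis of impaired yes/no. If 10% were impaired beforehand (assumed), that is about 3 of 28 per arm, and cells may be too sparse.

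The cost is a few lines of text and one degree of freedom per model for a single-term covariate. No further patient assessment is needed. The downside is little or no gain, and at 20 per arm a trivial loss, if the item turns out to be a rarely positive yes/no.

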#### **Quantitative assessment of sleep**

- Polysomnography, will be performed on day 3 after randomization to ensure the clearance of drugs that could alter the architecture of sleep. A portable device will be used (Nox A1 System®, Reykjavík, Iceland). Recording will last 9 h, starting at 10:00 p.m. and ending at 07:00 a.m. PSG will include electroencephalography (EEG) with electrodes placed at O1/A2 and C4/A1 according to the international 10-20 system, electromyography (electrodes will be located on the levator menti muscle), electrooculography (left superior canthus, right inferior canthus), electrocardiography, and pulse oximetry will be recorded. PSG will report sleep efficiency, total sleep time, latency, proportion of different stages of sleep, presence of sleep fragmentation, presence of micro-arousals, presence of apneas, registration of eye and limb movements. Sleep recordings will be visually scored by a sleep

specialist physician blinded to the group assignment using international criteria (66). Although PSG is the gold standard for evaluating sleep, because it is a complex and expensive exam, it will only be done once on day 3.

- Actigraphy, is the continuous measurement of an individual's movement using a wristwatch-like device (ACT-Trust® AT0503, Sao Paulo, Brazil). It is an objective method of quantifying sleep and circadian rhythm (67-69). All patients will have an actigraph placed on their non-dominant wrist immediately after randomization and until 1 week after ICU discharge. The main advantages of actigraphy compared to PSG are that it can be monitored continuously through several days, and the data registered is not intrinsically altered by medication (in contrast to EEG). Markers of sleep and circadian function derived from actigraphy include: circadian timing of each 24 hours of greatest activity (within each 24 hour period), sleep duration, sleep fragmentation, and regularity of circadian rhythmicity. All actigraphy data will be analyzed by a sleep physician blinded to the group assignment, using MATLAB (Mathworks, Natick, Massachusetts, USA).

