### ***Qualitative assessment of sleep***

- Richards-Campbell Sleep Questionnaire (RCSQ)(70): this is a five-item, visual analogue scale designed to assess the perception of sleep in patients who are critically ill. The scale evaluates perceptions of depth of sleep, sleep onset latency, number of awakenings, time spent awake and overall sleep quality. Patients will complete the questionnaire as they reflect on their previously night, starting from the second day of enrollment until ICU discharge.
- Pittsburgh Sleep Quality Index (PSQI)(71): the PSQI is a self-rated questionnaire, assessing sleep quality over a 1-month time interval. Nineteen individual items generate a seven-component score: subjective sleep quality, sleep latency, sleep duration, habitual sleep efficiency, sleep disturbances, use of sleeping medications and daytime dysfunction. The sum of scores for these seven components yields one global score. Patients will completed the questionnaire at 6 months post ICU discharge.

**Assessment of circadian rhythm :** Melatonin and cortisol plasmatic levels will be assessed at the day 1 and 3 after randomization. Four samples will be taken each day. Plasmatic melatonin levels will be measured with Melatonin ELISA Kit, according to the manufacturer's instructions (ABCAM, USA). Plasmatic cortisol levels will be analyzed in the laboratory of the University Hospital of the Pontificia Universidad Católica de Chile.

**Light and noise measurements:** A sonometer (Cirrus CR:172B, Cirrus Research, UK) and a luxometer will be placed near the patient's head. Ambient sound will be measured continuously and illuminance will be measured every 30 minutes until ICU discharge. These data will be registered and analyzed later by light and sound experts.

**ICU Delirium:** The presence of delirium will be evaluated once daily using the Confusion Assessment Method for the ICU (CAM-ICU)(72) starting immediately after randomization and until ICU discharge. Prevalence of delirium will be defined as the presence of delirium (positive CAM-ICU screening) on at least 1 day during ICU stay. Duration of delirium will be defined as total days of delirium during ICU stay.

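### For outcomes measured over time, the named repeated-measures methods do not target the arm difference, and they do not suit a daily sleep questionnaire that ends at ICU discharge

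*Protocol*

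**What the plan says.** Protocol section g, Sample size and statistical analysis, gives three methods for continuous outcomes:

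- Between arms: "Specific statistical analysis for comparisons between groups will be performed by Student's-t test or Mann-Whitney U-test for continuous variables".
- Over time: "Changes along time will be analyzed by one-way (repeated-measures) analysis of variance (ANOVA) or Friedman test".
- Arm by time: "Interactions between groups and time we will assessed with two-way repeated-measures ANOVA".

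The section sets intention to treat as the general principle. It does not say which of the three methods serves which repeated outcome.

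The schedules are given under the assessment headings:

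- RCSQ is completed daily, "starting from the second day of enrollment until ICU discharge".
- For hormones, "Melatonin and cortisol plasmatic levels will be assessed at the day 1 and 3 after randomization", with four samples on each day.
- The actigraph is worn "immediately after randomization and until 1 week after ICU discharge".
- For depression, "The BDI-II will be performed at hospital discharge and 6 months after ICU discharge". RBANS follows the same two times.
- CAM-ICU is done once daily, "starting immediately after randomization and until ICU discharge", but delirium is defined as one prevalence and one total of days per patient.

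**The concern.** The Specific goals are all comparisons of the intervention with standard care. For data over time, however, the only quantity named that involves the arms is the interaction. If that interaction were read as the treatment effect, a steady benefit on sleep perception, depression or cognition could be reported as no effect. The one-way and Friedman tests ask whether values change with time. Run within each arm, they invite a comparison of two p-values in place of a comparison of arms.

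A separate problem concerns RCSQ. Friedman and classical repeated-measures ANOVA need the same set of times from every patient, but the number of RCSQ days depends on how long each patient stays. Keeping only complete series would select on ICU stay, which is a post-randomisation event that the intervention might itself affect.

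**Working it through.** **Inputs.** The plan gives no power or effect figure for any repeated outcome, so there is none to reproduce. From the Protocol I take 56 patients at 1:1, that is 28 per arm, and alpha 5%. Whether 56 is the right number for the primary outcome is a different question. Effect size, within-patient correlation and ICU stay are not given for these outcomes and are assumed below.

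**Step 1: which outcomes have a pre-randomisation value, and which are cut short by ICU discharge.**

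| Outcome | First value | Last value | Cut short by ICU discharge? |
|---|---|---|---|
| RCSQ | second day | ICU discharge | yes |
| Melatonin, cortisol | day 1 | day 3 | only if the patient leaves by day 3 |
| Actigraphy | just after randomisation | one week past ICU discharge | length varies, but it does not stop at discharge |
| BDI-II, RBANS | hospital discharge | 6 months | no; lost through death or loss to follow-up |
| Delirium | one summary per patient | – | not analysed as a series |
| PSG (primary) | day 3 only | – | not repeated |

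None has a scheduled pre-randomisation value.

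**Step 2: what the interaction tests.** Let d(t) be the arm difference at time t. The interaction null is that d(1) = d(2) = … = d(K). If d(t) equals the same non-zero value at every time, that null is true and the test rejects with probability alpha. This follows from the structure and does not depend on K, the correlation or the effect size.

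**Step 3: what the average arm difference would detect.** With compound symmetry and correlation r, in SD units, SE = √{(2/n) × [1 + (K − 1)r]/K}. For K = 2, r = 0.6, n = 28 per arm and a constant effect of 0.6 SD:

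- SE = √(0.8 × 2/28) = 0.239
- 0.6/0.239 = 2.51
- power ≈ Φ(2.51 − 1.96) = Φ(0.55) ≈ 71%

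Simulations with 4,000 runs per setting and 28 per arm gave:

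| Arm difference over time | K | r | Interaction rejects | Group effect rejects |
|---|---|---|---|---|
| constant 0.6 SD | 2 | 0.6 | 4.9% | 69.3% |
| constant 0.5 SD | 5 | 0.5 | 5.2% | 66.1% |
| constant 0.8 SD | 2, 5, 8 | 0.3 to 0.7 | 4.5% to 5.2% | 89% to 99.8% |
| rising from 0 to 0.8 SD | 5 | 0.5 | 75.8% | 48.6% |
| 0 at a pre-randomisation time, then 0.8 SD | 2 | 0.5 | 83.2% | 39.4% |
| 0 at a pre-randomisation time, then 0.8 SD | 6 | 0.5 | 85.0% | 89.5% |

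The last two rows show that the interaction does carry a sustained treatment effect when the series includes a pre-randomisation value. Here it does not.

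**Step 4: complete RCSQ series.** Assume an exponential remaining ICU stay with median m days. The number still in ICU on day D is then 56 × 0.5^(D/m).

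| Median m | Day 3 | Day 7 | Day 14 | Day 30 |
|---|---|---|---|---|
| 4 days | 33.3 | 16.6 | 4.9 | 0.3 |
| 12 days | 47.1 | 37.4 | 24.9 | 9.9 |

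An analysis needing equal series must either drop the patients who leave early or cut everyone back to the shortest stay.

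**The case against.** The strongest reply is that the treatment comparison is already planned. The sentence before the two time-related ones assigns Student's t or Mann-Whitney to comparisons between arms, and a two-way ANOVA also yields a group main effect. On this reading the interaction is an extra, and its 5% rejection rate under a constant difference holds by construction. This stands. A reader might infer that the plan as a whole is blind to a sustained benefit, and the Protocol does not support that. It leaves open which result is the treatment effect for a repeated outcome. A t-test on daily RCSQ has no stated day, window or summary.

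Three further points narrow the scope:

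- BDI-II and RBANS are largely covered. The Specific goals and Secondary outcomes set neuropsychological impairment at 6 months, and a two-sample test at that time is a sound comparison.
- The hormone outcome is oscillation, with four samples a day. A group-by-time-of-day interaction is a legitimate test of whether the profile shape differs. The day-1 samples may also be nearly pre-treatment, because the care-activity component starts the day after inclusion and sampling times are not stated.
- Truncation at ICU discharge should not be read as affecting all repeated outcomes. It clearly applies only to RCSQ.

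It can also be said that matching tests to outcomes belongs in a statistical analysis plan. That is fair for the missing detail. But the Protocol itself names Friedman and repeated-measures ANOVA, and these do not fit a series of patient-dependent length.

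**Conclusion.** The point holds in a limited form, as a cheap improvement to secondary analyses. The named interaction should not be read as the treatment effect: without a pre-randomisation value it rejects at about 5% for a sustained benefit, whatever its size. Other planned tests could detect that benefit, with about 66% to 99.8% power for the group effect under the assumed 0.5 to 0.8 SD, but they are not tied to these outcomes. The interaction is not useless, since it does better than the group effect when the difference grows over time.

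The firmest part is RCSQ. Complete-series methods would rest on roughly 17 to 37 of 56 patients by day 7 and 5 to 25 by day 14, if the median remaining stay is 4 to 12 days and exponential. That selection conflicts with intention to treat. A reader might infer that the plan commits to a complete-case RCSQ analysis. It does not say so; the conflict arises if the named methods are applied to the daily series. The primary PSG outcome is measured once and is unaffected.

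**What to change.** In section g:

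- **RCSQ:** replace repeated-measures ANOVA and Friedman with a linear mixed model on all available observations (arm, time, arm by time, within-patient covariance). Report the arm difference averaged over a fixed early window, for example the first 7 ICU nights, and state how discharge and death are handled.
- **BDI-II and RBANS:** name the between-arm difference at 6 months as the reported effect.
- **Interaction tests:** keep them as supplementary, except where the question is the shape of the hormone profile within a day.
- **Within-arm p-values:** do not use them as evidence of effect.

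This changes wording only. The cost is slightly more modelling work and a missing-at-random assumption about discharge and death, which should be stated. The blood-sampling schedule, visits and sample size need no change.
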